### Assignment of interventions: allocation

#### Sequence generation {16a}

A block randomization with the help of computer-generated random numbers is performed to ensure that the number of participants in the study groups is approximately equal. Outpatients and inpatients are randomized separately.

#### Concealment mechanism {16b}

Allocation concealment is ensured as the computer-generated randomization code will not be released until the patient has been recruited into the trial. This serves to avoid a selection bias [21].

#### Implementation {16c}

The subinvestigators perform computerized randomization once the patient has consented to participate and then assign the patient to the treatment group accordingly.

### Assignment of interventions: blinding

#### Who will be blinded {17a}

A triple-blinded design is used. The participants will not be aware if they are in the control or AdhCare group. The study personnel assessing the outcome parameter as well as the data analyst are blinded as well.

#### Procedure for unblinding if needed {17b}

The persons administering the cognitive or behavioral intervention are not blinded, so there will be no unblinding. In later phases, as well as at the scheduled follow-up, unblinding is not required because all patients, regardless of group, receive support and assistance for adverse events and problems that arise (which may or may not be due to the intervention).

### Data collection and management

#### Plans for assessment and collection of outcomes {18a}

In the study, paper questionnaires are administered. Trained staff collects PD-related data and data on remaining pill counts and verifies the test results. Table 4 provides an overview of the questionnaires used.

**Table 4 Tab4:** Overview of the used questionnaires

Score	Cronbach’s alpha	Validity (correlation coefficient *r*)
GAI [22]	0.91	0.57–0.70^a^
MDS-UPDRS [23]	0.79–0.93 across parts	0.76–0.96 across parts^a^
MoCA [24]	0.83	0.61^a^
PDQ-8 [25]	0.80	0.47–0.61^b^
PHQ-9 [26]	0.89	0.55^b^

^a^Concurrent validity

^b^Construct validity

#### Plans to promote participant retention and complete follow-up {18b}

Plans to promote participant retention and full follow-up include detailed education of participants about the study timeline and number of consults. They get written information about their next scheduled appointments and assignments. In addition, our study team is instructed to promote successful study completion through their communication style during data collection. Also, the study team contacts participants to ensure data collection via telephone.

#### Data management {19}

A comprehensive data management plan is implemented to ensure data quality, security, and storage. This includes using standardized templates and guidelines for data entry, conducting regular quality checks and validation procedures, and implementing strict protocols for data security and storage. Data are collected by trained study staff and entered into a dedicated study database (by the same person). This guarantees a secure and direct transfer of data to the study office without any intermediary steps. Additionally, regularly conducted checks ensure the detection of any potential duplicate records and verification of value ranges.

#### Confidentiality {27}

Personal information about potential and enrolled participants is collected, shared, and retained by means of an identifier so that patients can only be matched to the identifier by the study investigators during the study. After completion of the study, only the data with the identifier are used to maintain confidentiality. The data are stored in a password-protected manner on the clinic’s internal drive. The individual trial identification numbers are numbered consecutively in ascending order starting with AC001.

Ensuring the appropriate level of anonymity, confidentiality, and de-identification when maintaining human subject data is crucial for reducing the risk potential for participants, researchers, and the university in alignment with the General Data Protection Regulation (GDPR) of the European Union. All trial data are recorded, processed, handled, and stored without disclosing the personal data of the subjects, so that they can be accurately reported, interpreted, and verified, while protecting the confidentiality of the records and the personal data of the subjects in accordance with the applicable law on the protection of personal data. Appropriate technical and organizational measures are in place to safeguard processed information and personal data from unauthorized or unlawful access, disclosure, dissemination, alteration, or destruction, including accidental loss, particularly when the processing entails transmission over a network.

#### Plans for collection, laboratory evaluation, and storage of biological specimens for genetic or molecular analysis in this trial/future use {33}

Plans for collection, laboratory evaluation, and storage of biological samples for genetic or molecular analyses are not necessary for the study because no biological samples are collected.

## Statistical methods

### Statistical methods for primary and secondary outcomes {20a}

Analysis will take place after full recruitment and follow-up. There are no planned interim analyses for efficacy. Statistical analysis will be tested at the 2-sided 5% significance level with any estimates displayed with 95% confidence intervals (CIs). The mean, standard deviation, and any other statistics other than quantiles will be reported to one decimal place greater than the original data. Quantiles, such as median, or minimum and maximum will use the same number of decimal places as the original data. All outcomes will be presented using descriptive statistics: normally distributed data by the mean and standard deviation (SD) and skewed distributions by the median and interquartile range (IQR). Binary and categorical variables will be presented using counts and percentages.

Baseline characteristics of the study population will be summarized separately within each randomized group using means (with standard deviations), medians (with interquartile ranges), and numbers (with percentages) where appropriate. Baseline characteristics will also be presented for dropouts and completers within each treatment group. Similarly, the primary and secondary outcomes at baseline and all follow-up by treatment groups will be described.

Further analyses will be conducted on all the primary and secondary outcomes. These will be performed based on the intention-to-treat principle and will utilize all available follow-up data from all randomized participants. For the main analysis of treatment effects, crude change in outcomes for both groups from baseline to follow-up will be provided as the mean change scores with standard deviations or proportions, and the corresponding 95% confidence interval (CI) will be presented. The primary outcome (motor function) will be analyzed with a linear mixed effects model. Study subjects will be considered as random effects. Treatment (control or AdhCare group), month (baseline and 3 and 6 months), setting (outpatient and inpatient), and the interaction of treatment with months will be considered as fixed effects. The baseline value of the motor function will be included as a covariate.

Secondary continuous outcomes will be analyzed analogously. However, there will be no adjustment for multiplicity of testing among effect estimates and corresponding 95% CIs for nonprimary outcomes, which therefore should be interpreted cautiously as hypothesis-generating results.

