### Outcomes {12}

#### Primary outcome

Because the overall goal is to improve patient-reported outcomes, the primary endpoint is motor function, which is assessed using the combined MDS revised Unified Parkinson’s Disease Rating Scale (MDS-UPDRS) II and MDS-UPDRS III after 6 months in the control versus AdhCare arm (intent-to-treat).

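### The primary mixed model uses the baseline motor score as both a response and a covariate, so the 6-month test either runs at about 10–15% type I error instead of 5% or loses its baseline adjustment

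*Protocol article*

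**What the plan says.** The Primary outcome section sets the endpoint as motor function, combined MDS-UPDRS II and III, "after 6 months in the control versus AdhCare arm (intent-to-treat").

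The section Statistical methods for primary and secondary outcomes {20a} then fixes the analysis:

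- Model: "The primary outcome (motor function) will be analyzed with a linear mixed effects model".
- Random part: "Study subjects will be considered as random effects".
- Fixed effects: "Treatment (control or AdhCare group), month (baseline and 3 and 6 months), setting (outpatient and inpatient), and the interaction of treatment with months".
- Covariate: "The baseline value of the motor function will be included as a covariate".
- Error rate: "Statistical analysis will be tested at the 2-sided 5% significance level", with 95% confidence intervals.

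The same section also says "For the main analysis of treatment effects, crude change in outcomes for both groups from baseline to follow-up will be provided". It does not say which model term or contrast is the 6-month treatment effect.

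**The concern.** A mixed model has a baseline level of month only if baseline scores are among the outcome rows. Entering the same score as a covariate makes those rows nearly self-predicting. A single slope is fitted across all three visits, so it is pulled toward 1. The almost-zero residuals at baseline are then averaged into the variance that sets the standard error at 6 months.

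Three treatment effects can be read from such a model, and each is a problem for the stated endpoint:

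- **Adjusted difference at month 6:** its standard error is too small.
- **Treatment-by-month-6 interaction:** it is no longer adjusted for baseline.
- **Effect averaged over months:** it includes the baseline month, where randomisation makes the expected difference zero.

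At stake are the nominal 5% level and the 95% interval of the primary result. Because no contrast is named, the choice among these could be made after the data are seen. Section {20a} has the secondary continuous outcomes analysed in the same way, so the problem carries over to them.

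**Working it through.** **Inputs from the protocol.** Response times 0, 3 and 6 months; treatment, month, treatment × month and setting as fixed effects; baseline covariate; random subject effect, taken as a random intercept with constant residual variance; two-sided 5% (all from {20a}). From Sample size {14}: difference 5, SD 8.8, 51 per arm evaluable, 64 per arm after allowing for 25% dropout.

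**Assumed.** The correlations between visits. The protocol gives none, so a range is shown.

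**The plan's own figure.** A two-sided t-test with 51 per arm, difference 5 and SD 8.8 has power 81.1% (noncentral t), against 80.750% stated. The design inputs are therefore read correctly.

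**Adjusted difference at month 6.** Set the variance to 1 at each visit, with correlations r03, r06 and r36. With complete data and a large sample:

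- fitted baseline slope: b = (1 + r03 + r06)/3, which is (1 + 2r)/3 when all correlations equal r
- residual variance at baseline: (1 − b)²
- residual variance at month t: 1 + b² − 2b·r0t
- variance the model uses at month 6: the mean of the three residual variances
- true variance at month 6: 1 + b² − 2b·r06
- type I error: 2[1 − Φ(1.96 × model SE / true SE)]

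At equal r = 0.7, b = 2.4/3 = 0.80. The residual variances are 0.04, 0.52 and 0.52, with mean 1.08/3 = 0.36. The SE ratio is √(0.36/0.52) = 0.83 and the type I error is 10.3%.

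| Correlations (r03/r06/r36) | b | Model variance | True variance | SE ratio | Type I error |
|---|---|---|---|---|---|
| 0.4 equal | 0.600 | 0.640 | 0.880 | 0.85 | 9.5% |
| 0.5 equal | 0.667 | 0.556 | 0.778 | 0.85 | 9.8% |
| 0.7 equal | 0.800 | 0.360 | 0.520 | 0.83 | 10.3% |
| 0.9 equal | 0.933 | 0.129 | 0.191 | 0.82 | 10.7% |
| 0.8/0.7/0.8 | 0.833 | 0.306 | 0.528 | 0.76 | 13.6% |
| 0.85/0.75/0.85 | 0.867 | 0.249 | 0.451 | 0.74 | 14.5% |

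**Simulation check.** REML fits with no treatment effect, 2,000 trials per scenario:

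- 51 per arm, complete data: 9.8–11.4% with equal correlation, 13.2–15.0% with decaying correlation.
- 64 per arm, 25% dropout: 10.4–12.1% and 16.0–16.3%.

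**Interaction at month 6.** The covariate is constant within a patient, so with complete data it cancels from the change from baseline.

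- *Precision.* The variance relative to baseline-adjusted analysis is 2(1 − r)/(1 − r²) = 2/(1 + r), which is 1.33 at r = 0.5 and 1.18 at r = 0.7. With 51 per arm and SD 8.8, the SE is 1.74 against 1.51 at r = 0.5, and 1.35 against 1.25 at r = 0.7. Power for 5 points at r = 0.5 is 82% against 91%.
- *Error rate.* With equal correlation it is 5.0%. At 0.8/0.7/0.8 the model uses 2 × (0.2 + 0.3 + 0.2)/3 = 0.467, whereas the true variance of the change is 2 × 0.3 = 0.600. The SE ratio is 0.88 and the type I error 8.4%. At 0.85/0.75/0.85 it is 9.3%.

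**Effect averaged over months.** A true 5 points at both follow-ups is returned as (0 + 5 + 5)/3 = 3.3. A true 2.5 then 5 is returned as (0 + 2.5 + 5)/3 = 2.5.

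**Secondary outcomes.** For SAMS, assessed at baseline and 6 months only (Table 2), b = (1 + r)/2. The same algebra gives about 15–16% for the adjusted 6-month contrast at r from 0.4 to 0.9.

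**The case against.** **The inflated error rate belongs to a contrast the protocol never names.** With baseline as a month level, the interaction at month 6 is at least as natural a test. It is unbiased under randomisation and keeps 5% under equal correlation. At r = 0.5 its 82% power still meets the planned 80.75%, because the sample size rests on an unadjusted t-test. This stands as far as it goes: on that reading with equal correlation, the cost is lost precision and not a broken test. But the specified covariate then does nothing, and the level drifts to about 8–9% if correlation decays.

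**Part of the 14–15% comes from the random-intercept structure.** This also stands. A model with months 3 and 6 as response and baseline as covariate, but still only a random intercept, gave 6.7–8.2% under decaying correlation and 4.5–5.8% under equal correlation. The double use of baseline alone accounts for roughly 9–11%.

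**Other text suggests that only follow-up visits were meant as response.** Section {20a} speaks of using the available follow-up data, and the primary-outcome row of Table 2 marks 3 and 6 months only. If that was the intent, the model sentence contradicts it. Table 2 also records MDS-UPDRS II and III at baseline, so the rows will be there for an analyst who follows that sentence.

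**Nobody proposed a month-averaged effect.** True. It is a side point, and the conclusion does not depend on it.

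**Such detail can wait for an analysis plan.** The contrast and the covariance could. But the article itself fixes response times, fixed effects, random effect and covariate, and these conflict.

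**Conclusion.** The concern holds. As specified, the primary model cannot give a baseline-adjusted 6-month comparison at the stated two-sided 5% level. The adjusted month-6 difference has a type I error of about 9.5–10.7% for equal correlations of 0.4–0.9, and about 13.6–14.5% for the decaying patterns tabulated. The interaction keeps 5% only under equal correlation, and it forgoes the baseline adjustment.

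These sizes assume a random intercept with constant residual variance, which is the plain reading of the text, and correlations that the protocol does not supply. The exact excess depends on them, but its direction and the approximate doubling do not over the range examined. Since this is the primary test and its confidence interval, the correction should be made before the data are analysed.

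**What to change.** Rewrite the model sentence in {20a}:

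- Response: MDS-UPDRS II+III at months 3 and 6 only.
- Fixed effects: treatment, month (3, 6), treatment × month, setting, baseline score and baseline × month.
- Covariance: unstructured within subject. This also removes the residual inflation under decaying correlation that dropping the baseline rows alone would leave.
- Primary test: the treatment contrast at month 6, two-sided 5%, with its 95% confidence interval.
- Label the crude within-group changes as descriptive, so that they are not taken for the main treatment comparison.

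An equally valid alternative keeps baseline as a response, drops the covariate and constrains the two arms to a common baseline mean, with the same named contrast. Choose one and apply it to the secondary continuous outcomes as well; for an outcome with a single follow-up, the first option reduces to a baseline-adjusted comparison at 6 months.

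The cost is a few words in the analysis section before database lock. No new data, visits or patients are needed.

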### Interim analyses {21b}

Interim analyses are not included in this study. Early discontinuation is also not planned due to the study design.

### Methods for additional analyses (e.g., subgroup analyses) {20b}

Additional analyses are not planned.

### Methods in analysis to handle protocol nonadherence and any statistical methods to handle missing data {20c}

The data are captured in the electronic case report form and will be transferred anonymously from this to the statistician for processing (i.e., statistical analysis). Automated checks will be implemented, and manual checks will be done against the data to ensure completeness and consistency of data. The database and check programming will be validated prior to implementation. Data identified as erroneous or inconsistent, or key data that are missing, will be referred to the subinvestigators and to the principal investigator for clarification. After these forms are returned, the data will be corrected as required. All modifications to the data will be logged in the audit trail. Prior to the closure of the database, an audit of the raw data will be performed. All errors detected during the audit will be corrected prior to database closure. Visual and computerized methods of data validation will be applied in order to ensure accurate, consistent, and reliable data for the subsequent statistical analysis. These procedures aim to detect out-of-range values, contradictory data, abnormal evolutions over time, and possible protocol deviations (eligibility criteria, time, and medication adherence, etc.).

The sensitivities of all treatment effect estimates to missing outcome data will be explored; these models will explore the robustness of the treatment estimates to whatever small amount of missing data there is. The main analysis will use all available data that we believe are valid under the assumption of missing at random (see primary outcome analysis above). We will then use a suite of sensitivity analysis to explore the robustness of the primary analysis to departures from assumptions, including all randomized participants. If required, sensitivity analyses will include multiple imputation and imputing a range of values for missing data under missing not at random assumptions.

### Plans to give access to the full protocol, participant-level data, and statistical code {31c}

Granting public access to the full protocol, participant-level data set, and statistical code is not currently anticipated but can all be obtained from the author.

### Oversight and monitoring

#### Composition of the coordinating center and trial steering committee {5d}

The research team encompasses a range of expertise, including behavioral and medical management, research design, multicenter data collection, epidemiology and biostatistics, patient engagement, practice transformation, continuing education, quantitative outcomes assessment, and qualitative analysis of processes and outcomes. We did not establish a trail steering committee or Stakeholder and Public Involvement Group in the context of this study.

#### Composition of the data monitoring committee, its role, and reporting structure {21a}

A data monitoring committee is not necessary, and not required by the local ethics committee, due to the short duration and the known minimal risks in this kind of cognitive- and behavioral-focused intervention.

#### Adverse event reporting and harms {22}

Inadequate knowledge, skills, and experience among trained study staff can lead to adverse events such as personal insult, frustration, loss of motivation, emotional distress, and loss of trust being linked to inappropriate practices. If participants report adverse events of any kind, it will be recorded, assessed internally by the team to prevent future adverse events, and reported as part of the planned publication.

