#### Trial design {8}

This study is based on the NeuGerAd study, a longitudinal observational study of adherence in older adults with neurological disorders [19]. The AdhCare trial is designed as a randomized, controlled, patient, observer, and data analyst-blinded superiority trial with two parallel groups and a primary endpoint of motoric function using UPDRS II and III. It is conducted to test the efficacy of AdhCare, a tailored intervention to enhance adherence compared with that achieved using routine care. The participants are assessed at baseline and at 3 and 6 months of follow-up.

A total of 130 participants are randomized in a 1:1 ratio: intervention in the AdhCare arm (*n* = 64) or control group with standard of care (*n* = 64).

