#### Intervention description {11a}

Participants with any degree of nonadherence according to SAMS (SAMS ≥ 1) are randomized to the control arm or the AdhCare intervention arm. As it has been shown that implementation of fewer intervention strategies (in one patient) leads to better adherence outcomes [11], our approach is a tailored intervention that is adapted to the main reason for the individual patients’ nonadherence according to a self-reported adherence measure. Therefore, depending on the main reason for nonadherence according to SAMS (modifications, missing knowledge, and forgetfulness), the participants in the AdhCare arm receive a cognitive- or behavioral-focused intervention (Table 1).

**Table 1 Tab1:** Tailored intervention

Reason for nonadherence	Approach/focus	Particulars
1 Modifications	Educational/alternating strategies, e.g., adjusting the medication regimen	Addressing barriers Physician providing further treatment strongly involved
2 Missing knowledge	Informational/educational strategies to enhance knowledge, also about disease-related risks	Further sources of information are named
3 Forgetfulness	Behavioral: habit-based medication-taking reminders	Strong involvement of a life partner, if possible

The following interventions are provided to the AdhCare (intervention) group:

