A standardized, informational talk to improve patient empowerment to take responsibility and control of their own health. Depending on the main reason for their nonadherence, we, among other things, perform the following interventions:Modifications: explain the medication, discuss barriers, and strive for patient empowerment to discover ways to improve the medication regimen and emphasize different ways of dealing with emerging problems other than cutting out on medications for instanceMissing knowledge: explain the medication and its indications, provide information about individual risks, and indicate other sources of informationForgetfulness: present and apply habit-based techniques to help the patient remember to take the medication and strive for patient empowerment to improve the medication regimenA written summary of the most significant aspects for their individual improvement of adherence.Their physician, who continue to provide treatment, are contacted and informed about the study, individual patients’ adherence problems and barriers, and possible strategies to minimize nonadherence in the particular patient.A follow-up telephone call to reinforce the respective focus about the medications and adherence after 2 weeks.

The control group received standard information about the course and therapy of PD.

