#### Participant timeline {13}

At baseline and follow-up, the participants complete a staff-administered assessment and a self-report paper-based assessment. These assessments are summarized in Table 2. The time schedule is summarized in Table 3.

**Table 3 Tab3:** Time schedule

Time point	Study period			
	Enrollment, *-t*_*1*_	Allocation, 0	Post-allocation, *3 months*	Close-out, *6 months*
Enrollment				
Eligibility screen	X			
Informed consent	X			
Allocation		X		
Interventions				
*[AdhCare]*		X Cognitive- or behavioral-focused intervention		
*[Control]*		Standard information about the course and therapy		

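### Adverse events are recorded when participants report them, but only the AdhCare arm has a scheduled 2-week call, so published harm counts by arm are at risk of unequal ascertainment (minor)

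*Protocol article*

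**What the plan says.** All references are to the protocol article.

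- **Capture.** Adverse event reporting and harms {22} states the rule: "If participants report adverse events of any kind, it will be recorded". The events are then "assessed internally by the team to prevent future adverse events, and reported as part of the planned publication".
- **Schedule.** Table 2 (Outcomes {12}) lists the measures by visit and contains no adverse-event item.
- **AdhCare contacts.** Intervention description {11a} opens its list with "The following interventions are provided to the AdhCare (intervention) group". The last item is "A follow-up telephone call to reinforce the respective focus about the medications and adherence after 2 weeks".
- **Control contacts.** The same section says "The control group received standard information about the course and therapy of PD". Table 3 (Participant timeline {13}) shows for this arm only "Standard information about the course and therapy", at allocation. No 2-week call is listed.
- **Contacts common to both arms.** Trial design {8}: "The participants are assessed at baseline and at 3 and 6 months of follow-up". Reminder calls before appointments (Strategies to improve adherence to interventions {11c}) and telephone contacts for data collection (retention section {18b}) are not limited to one arm.
- **Support.** Procedure for unblinding {17b} says "all patients, regardless of group, receive support and assistance for adverse events and problems that arise". That promises equal help. It does not say that both arms are asked about events equally.

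**The concern.** When recording depends on the participant speaking up, the number of events recorded depends on how often the participant has someone to tell. Here that differs by design. The harms that section {22} names are reactions to dealings with study staff, such as frustration, distress and loss of trust. The AdhCare talk takes place at allocation, so the 2-week call is the first scheduled contact after it. A control participant's first scheduled assessment comes at 3 months.

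The call is also part of an intervention whose providers are not blinded, whereas outcome assessors are. The article does not say who makes the call, but events heard there may reach the record through staff who know the allocation.

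What is at stake is how the published harms are read. In a two-arm trial readers will set the counts side by side, and some of any AdhCare excess could come from the extra contact.

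**Working it through.** The article gives no adverse-event rate and no reporting probability, so there is no figure of the plan to reproduce. The calculation shows only how far unequal contact could move the counts.

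**Inputs from the article**
- Scheduled contacts after allocation: AdhCare 3 (2 weeks, 3 months, 6 months); control 2 (3 and 6 months).
- 64 participants per arm (Sample size {14}).

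**Assumptions, not in the article**
- True harm is equal in the two arms.
- Every event is present before week 2 and can still be reported until the participant mentions it.
- At each contact an unreported event is mentioned with the same probability p in both arms.
- For counts only: a true event rate of 20%, so 64 × 0.20 = 12.8 true events per arm.

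**Formulas**
- Share of true events reported: AdhCare 1 − (1 − p)³; control 1 − (1 − p)².
- Apparent ratio: the first divided by the second.
- Expected excess in AdhCare: 12.8 × p(1 − p)², since the two shares differ by p(1 − p)².

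| p | AdhCare share | Control share | Ratio | Excess events |
|---|---|---|---|---|
| 0.1 | 0.271 | 0.190 | 1.43 | 1.0 |
| 0.2 | 0.488 | 0.360 | 1.36 | 1.6 |
| 0.5 | 0.875 | 0.750 | 1.17 | 1.6 |
| 0.8 | 0.992 | 0.960 | 1.03 | 0.4 |
| 1.0 | 1.000 | 1.000 | 1.00 | 0 |

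**Limits.** As p approaches 0 the ratio approaches 3/2 = 1.5. The excess is largest at p = 1/3, where p(1 − p)² = 4/27 = 0.148 and 12.8 × 0.148 = 1.9 events. It scales with the assumed 20% rate.

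**Effect of the shared calls.** Suppose one reminder call before each of the two visits also counts as an opportunity in both arms. Contacts become 5 and 4, and the limiting ratio falls to 5/4 = 1.25. At p = 0.1 it is 0.410/0.344 = 1.19. Data-collection calls made in both arms would lower it further.

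**Timing of events.** Only events present by the 2-week call gain from the extra contact. Events that begin later meet the same scheduled contacts in both arms, so the table shows the case least favourable to the plan under this model.

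**Check on the remedy.** If counts use the same number of contacts in both arms, the two shares are equal and the ratio is 1.00 for every p.

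**The case against.** Much of the opposing case stands.

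- **No harm comparison is planned.** A reader might infer that a planned between-arm harm result is biased. The article does not support that. Harms are not a listed outcome, the statistical methods cover primary and secondary outcomes, and no additional analyses are planned. The article says only that events will be reported.
- **The wording does not exclude a question.** A reader might infer that events count only when volunteered unprompted. The wording would also cover answers to a question, and the full protocol, which is not shown, may contain one. The 2-week call is described as reinforcement. Nothing says that events are asked about or recorded there.
- **This is not the only safety-relevant information.** There is no data monitoring committee, for which the article gives reasons (short duration, minimal known risk, no ethics committee requirement). But Table 2 schedules PHQ-9 and GAI at baseline and 6 months and MDS-UPDRS IV at baseline, 3 and 6 months, without distinction by arm. PHQ-9 and GAI bear on emotional distress, one of the named harms. They do not replace event capture.
- **Larger numbers can be produced, but only by assumption.** Suppose each contact brings a fresh, independent 10% chance of a report. Participants with at least one report are then 64 × 0.271 = 17.3 against 64 × 0.190 = 12.2. Nothing in the article supports that 10%, and it would mean that 19% to 27% of participants report an event in an intervention described as minimal risk.
- **The direction is not certain.** Contact alone points to more reports in AdhCare, but participants may hold back complaints about staff from those staff. The tailored talk is given to one arm, so equal true harm is itself doubtful for the named reactions.

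What survives is narrower: the published rule depends on the participant's report, and scheduled contact is unequal.

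**Conclusion.** The point holds as a risk, not as a demonstrated bias, and it is minor. As published, the plan ties recording to participant reports, commits to publishing the events, and gives one arm an extra scheduled contact (3 against 2). With equal true harm the apparent ratio lies between 1.00 and 1.5. With an assumed 20% true rate and 64 per arm, the expected excess is about 2 events at most. Both figures rest on an assumed reporting probability and on the persistent-event model, and calls shared by the arms reduce them. The primary and secondary outcome analyses are not affected.

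**What to change.** **For any remaining 3- and 6-month assessments:** state in section {22} and Table 2 that both arms are asked the same neutrally worded adverse-event question, covering the period since the previous assessment. Base by-arm counts on events captured at those common assessments.

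**For reporting:** list events first heard at the 2-week call, or volunteered at other times, separately from the by-arm counts. State that AdhCare had one more scheduled contact than control.

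**Timing.** Recruitment ended on 3 March 2023, and protocol version 2.0 is dated 14 August 2023. If visits ran to schedule, all 3-month assessments were due by about 3 June 2023. At the version date only participants recruited after about 14 February 2023 still had a 6-month assessment ahead. For nearly all participants the reporting step is therefore the part that still applies.

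**Cost.** One question at existing visits, one table row and one sentence; no new visit. The downsides are recall over 3 months, which is weak for passing reactions, and more minor events on record. Where no common question was asked, an event already mentioned at the 2-week call may not have been repeated at 3 months. The separate list should therefore stand beside the by-arm counts.
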